### Sample size assumption

Under the conditions of the trial, we assumed that the standard 6-month regimen has a 95% or higher sputum culture conversion rate and with estimated 92.5% of that for 4.5-month study regimen based on the published data. The study was designed to determine whether either of the shortened study regimens was not inferior to the control regimen and a margin of noninferiority of 5% was used. With the assumption that as many as 20% of patients will loss to follow-up or not be assessable in the primary analysis, and with the consideration of approximately 5.5% primary drug resistance prevalence, a total target sample size was 3900 patients (1300 subjects per group) would be required to demonstrate noninferiority, with a statistical power of 0.8 and an alpha level of 0.05 (one-sided). Participant recruitment began in August 2016 and is expected to finish in December 2018.

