**Methods:**

We are conducting a randomized, open-label, controlled, non-inferiority trial involving patients with smear-positive, newly diagnosed DS-PTB cases nationwide to assess the efficacy and safety of two 4.5- month regimens in comparison to the standard 6-month WHO recommended regimen. The regimen used in one experiment group is a 4.5-month fluoroquinolone-containing regimen, which consists of full course of levofloxacin, isoniazid (H), rifampin (R), parazinamid (Z) and ethambutol (E). Regimen used in the second experiment group includes 4.5-month full course of H, R, Z, E with levofloxacin removed. Patients in the control group, receive H, R, Z and E for 2 months, followed by 4 months of H and R. The primary endpoint is treatment failure or relapse within 24 month after treatment completion.

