## Discussion

Current 6-month regimens for new smear positive DS-PTB are used in more than 90 countries and are designed and evaluated cost-effective [13]. With the exciting results of shortened regimens for MDR-TB cases from the previous 24 months to 9 months length of therapy [14–16], researchers have been paving the way to explore the probably shorter regimens for DS-PTB inferior to the current standard ones. In the 1970s, the introduction of R resulted in a 15 to 20% increase of sputum conversion at 8 weeks and shortening duration of treatment from 18 months to 9 months. The later introduction of Z led to a further 13% increase of sputum conversion at 8 weeks, allowing therapy to be further reduced from 9 months to 6 months [17–20]. Based on these findings, Medical Research Council (MRC) led the controlled clinical trial of five short-course (4-month) chemotherapy regimens for PTB patients including 2HRSZ/2HRZ, 2HRSZ/2HR, 2HRSZ/2HZ, 2HRSZ/2H, 2HRZ/2H. However, all the shortened regimens failed to present expected primary outcome, instead, with 16%, 11%, 32%, 30% and 40% recurrence after 24 months of treatment completion [21, 22]. For years with new drugs progress for TB chemotherapy, especially the favorable pharmacodynamics and bactericidal activity of FQ on MTB, shortening the treatment duration for DS-PTB by using a FQ-based regimen is of great hot topic 3 independent shortening clinical trials have been reported simultaneously with a failure to show noninferiority to the 6-month standard regimen attributed to the higher recurrence rate observed with the 4-month regimens, despite rapid culture conversion during treatment [7–9]. These findings raised questions that the shortening FQ-containing regimens did not work as adequately as the murine model did which may overpredict the sterilizing potency of the regimens.

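### The sample size assumes culture conversion rates, but the deciding test is on failure or relapse by 24 months after treatment, so the stated 80% power is unsupported for the primary outcome

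*Protocol article*

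**What the plan says.** **Planning rates.** The Sample size assumption section assumes that "the standard 6-month regimen has a 95% or higher sputum culture conversion rate and with estimated 92.5% of that for 4.5-month study regimen", and cites published data without saying which. It adds that "a margin of noninferiority of 5% was used", with power 0.8 and a one-sided alpha of 0.05. Two allowances are named: "as many as 20% of patients will loss to follow-up or not be assessable in the primary analysis", and "approximately 5.5% primary drug resistance prevalence". The target is 1300 per group, 3900 in total.

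**Primary outcome.** The abstract says: "The primary endpoint is treatment failure or relapse within 24 month after treatment completion". The Outcome measures section gives the same composite by 24 months after the end of treatment. It also lists, as a further primary measure, treatment failure at 4.5 or 6 months after randomization. Failure is defined by a positive smear at the end of treatment, and relapse by at least one positive culture at scheduled visits over the next two years.

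**Test.** The Statistical analysis section applies the 5% margin to the difference in the proportion with a primary unfavourable outcome.

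**Place of conversion.** The Statistical analysis section lists culture conversion at 8 weeks and at treatment completion as secondary outcomes. The Outcome measures section also lists sputum conversion as secondary.

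**The concern.** The planning rates are worded for one outcome and the test is on another. A conversion rate measured on treatment contains no relapse, whereas the primary composite adds 24 months of post-treatment relapse. Relapse is where a shortened regimen is most likely to do worse.

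The article's Discussion makes the same distinction. It attributes the failure of three earlier fluoroquinolone trials to more recurrence on the 4-month regimens, although cultures had converted quickly on treatment. By that account, conversion should not stand in for the primary outcome without a justification, and none is given.

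What is at stake is the meaning of the power statement. A reader takes 80% as the chance that a regimen 2.5 points worse than control is declared noninferior. The document supplies no rates from which that chance can be worked out for failure or relapse.

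**Working it through.** **Inputs from the Sample size assumption section.** Rates 95% and 92.5%, read as absolute percentages; margin 0.05; one-sided alpha 0.05 (z = 1.645); power 0.80 (z = 0.842); allowances of 20% and 5.5%; 1300 per arm.

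**Step 1: the plan's own figure.** Treat the rates as if they belonged to the tested outcome (unfavourable 5% v 7.5%):

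n = (1.645 + 0.842)² × (0.05 × 0.95 + 0.075 × 0.925) / (0.05 − 0.025)² = 1157 assessable per arm after rounding up.

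With both allowances, 1157 / (0.80 × 0.945) = 1531 randomised per arm, or 1157 / 0.745 = 1554 if they are added. With the 20% loss alone it is 1447. The stated 1300 is not reproduced.

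**Step 2: assessable patients at 1300 per arm.** The article does not say how the allowances combine. If they multiply: 1300 × 0.80 × 0.945 = 983. If they add: 1300 × 0.745 = 968. With the 20% loss only: 1040.

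**Step 3: power on failure or relapse.** For unfavourable proportions pC (control) and pT (test), with n assessable per arm:

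power = Φ( [0.05 − (pT − pC)] / √{[pC(1 − pC) + pT(1 − pT)] / n} − 1.645 )

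Example, 8% v 10.5% at n = 983: the variance sum is 0.0736 + 0.093975 = 0.167575; the standard error is √(0.167575 / 983) = 0.01306; 0.025 / 0.01306 = 1.915; Φ(0.270) = 0.61.

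The document gives no failure or relapse rates, so the rates below are illustrative assumptions.

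| Control v test | Difference (points) | Power, n = 983 | Power, n = 1040 |
|---|---|---|---|
| 5% v 6% | 1 | 99% | 99% |
| 5% v 7.5% | 2.5 | 74% | 76% |
| 5% v 8% | 3 | 56% | 58% |
| 8% v 9% | 1 | 94% | 95% |
| 8% v 10.5% | 2.5 | 61% | 63% |
| 10% v 10% | 0 | 98% | 98% |
| 10% v 11% | 1 | 89% | 91% |
| 10% v 12.5% | 2.5 | 54% | 56% |

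**Step 4: separating two effects.** The 5% v 7.5% row uses the article's own numbers and gives 74%, not 80%. That gap comes from 1300 against 1531 and has nothing to do with the choice of outcome. The endpoint problem shows in the other rows. Keeping the 2.5-point difference and moving only the control rate from 5% to 10% takes power from 74% to 54%. A true difference of 1 point or less puts power above 80% in every row shown.

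All figures are for one experimental arm against control in one analysis population.

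**The case against.** **Conversion may be loose wording for favourable outcome.** The section gives no time point for conversion, uses the same 5% margin as the primary test, and speaks of patients not assessable in the primary analysis. The Outcome measures section defines a favourable outcome as negative cultures at the end of follow-up. This reading is possible, but the document does not state it, and it uses conversion elsewhere for a distinct secondary outcome. If it is what was meant, the paragraph is still wrong as written, and the 74% in step 4 applies.

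**End-of-treatment failure is also listed as primary.** This stands in part. End-of-treatment conversion is close to the complement of that measure, so the planning rates are not irrelevant to every primary measure. But that failure is defined by smear and contains no relapse, and the abstract names only the 24-month composite.

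**The article condenses a fuller protocol.** Detailed sources may sit there. The point is not an omission, however: the article does state its planning assumption, and states it for a different outcome.

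**Stronger readings that the document does not support.**
- A reader might infer that the trial is underpowered. The rates needed to show that are not given, and power exceeds 90% under several plausible assumptions.
- A reader might set the older 4-month regimens, "with 16%, 11%, 32%, 30% and 40% recurrence after 24 months of treatment completion", against the implied 7.5% and conclude that failure is near certain. Those are different regimens: none contains ethambutol or levofloxacin, and only the two with 16% and 11% keep rifampicin to the end. They call for an explanation; they do not predict this trial.
- A reader might infer that a negative result could not be told apart from low power. The decision rests on a confidence interval whose one-sided 5% half-width at 983 per arm is about 1.645 × 0.0109 = 1.8 points (5% v 7.5%) to 1.645 × 0.0142 = 2.3 points (10% v 12.5%). Against a 5-point margin, it would show whether a result is inconclusive or points to inferiority.

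**Conclusion.** The concern holds in this form: the 95% v 92.5% assumption is stated for culture conversion, a secondary outcome, while the 5-point test is on failure or relapse by 24 months after treatment. The 80% power is therefore unsupported for the primary test. It is not shown to be too high or too low. Under the illustrative rates in the table it runs from 54% to 99%, and the true difference matters most. If the planned 2.5-point deficit is kept, power at 983 per arm is 74% with 5% unfavourable in control and 54% with 10%.

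This rests on the two allowances multiplying (using only the 20% loss raises power by about 2 points in the 2.5- and 3-point rows) and on 92.5% being an absolute rate. Read as a fraction of 95%, it would be 0.925 × 0.95 = 87.9%, a difference of 7.1 points that exceeds the margin, so the absolute reading is the only workable one. The validity of the test, the margin and the endpoint definition are not affected.

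**What to change.** In the Sample size assumption section:

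1. Replace the conversion rates with the assumed proportion with failure or relapse by 24 months after treatment, separately for control, 4.5LfxHREZ and 4.5HREZ, each with its source. If 95% and 92.5% were meant as favourable-outcome rates, say so.
2. Explain how these proportions relate to the recurrence described in the Discussion, noting that the earlier regimens differ from those tested here.
3. Keep 3900 fixed and restate power on the primary outcome over a range, for example control 5% to 10% and a difference of 0 to 3 points. Say how the 20% and 5.5% allowances were combined, so that the 1300 per arm can be checked.

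The cost is a rewrite of one paragraph, with no change to enrolment or procedures. The downside is that the stated power may become less favourable.

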### Study patients

Adult patients who are newly diagnosed, previously untreated or treated less than 1 month with anti-TB drugs, are determined by chest X-ray with any abnormality consistent with TB and positive results of sputum smears on two occasions, with culture-confirmed susceptibility to H, R, E and Z and Lfx. All patients with written or witnessed oral informed consent were recruited if they met the trial eligibility criteria at screening. Detailed inclusion and exclusion criteria is provided in Table 1.

**Table 1 Tab1:** Eligibility criteria

Inclusion criteria	Exclusion criteria
Is willing and able to give informed consent to participate in the trial treatment and follow-up (signed or witnessed consent if the patient is illiterate)	Is HIV positive
Is aged of 18–65 years old	Is concomitant with mental disorders
Is previously untreated or treated less than 1 month with anti-TB drugs	Is concomitant with diabetes while mellitus blood glucose out of control
Has 2 positive sputum smear results for mycobacterium TB at screening	Is pregnant or breastfeeding
Has a chest X-ray abnormality compatible with a diagnosis of PTB	Has a prolonged QTcF^a^ (>480 ms)
Is not pregnant for female patient at bearing age and willing to use effective contraception during study period	Is currently participate in another trial of a medicinal product
Has CrCl^b^ > 30 ml/ min, HB^c^ > 7.0 g/dL and PLT^d^ > 50 × 10^9^/L at screening	Is concomitant with severe cardiovascular, hepatic, renal, nervous system, hematopoietic system injury and other diseases, or concomitant with neoplastic diseases
Has ALT^e^ and TBIL^f^ less than 2 times the upper limit of normal at screening	Has extensive lesion in the lung concomitant with respiratory insufficiency
	Has known allergy to any of the anti-TB drugs in the trial
	Is taking any medications contraindicated with the medicines in any trial regimen of the study

^a^
*QTcF* Fridericia-corrected QT, ^b^
*CrCl* creatinine clearance, ^c^
*HB* hemoglobin, ^*d*^
*PLT* Platelet, ^e^
*ALT* alanine aminotransferase, ^f^
*TBIL* total bilirubin

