Since Lfx administered with high dose is of comparable efficacy compared with Mfx and Gfx against MTB, it is possible to introduce Lfx to the regimen for shorter duration of DS-PTB. However, there is also concern that Lfx may fail as first-line anti-TB drugs because of its widely applied for common infections such as urinary and gastrointestinal tracts, wounds, and other lung infections. In high-TB-burden countries, a great number of cases with undiagnosed TB are likely to take an FQ, which could be selected for resistance in at least a fraction of MTB they harbor [23]. Several studies focus on FQ resistance and its association with previous FQ exposure indicated a low prevalence. Researchers from Korea found 2.6% FQ resistance in patients exposed to FQs while 3.4% resistance in patients without FQ exposure [24]. A study from Taiwan found no correlation of FQ resistance with either FQ exposure or duration of FQ exposure, but saw a positive correlation with previous anti-TB treatment and resistance to any other drugs [25]. Previous study from the same research team comparing sputum taken both before and after a course of FQs treatment showed that patients who received an FQ before standard anti-TB treatment had a poor prognosis, most likely as a result of the emergence of drug resistant. 11.1% of the MTB obtained FQ resistance after taking an FQ for 1–3 weeks [26]. The fifth national TB epidemiology survey in China of 2010 reported that Lfx resistant TB accounted for 9.1% among new TB patients [27]. A high prevalence of FQ-resistant TB may void the possibility of Lfx as first line drug for shortening DS-PTB treatment duration. Appropriate bacteriological and histopathological tests for TB should be performed as early as possible before Lfx-containing regimen is recommended. If the study regimen is successful, it is expected to provide a new standard of care for DS-PTB which would cut down the number of required clinic visits and the burden on the health care system and could also decrease the percentage of patients who fail to complete the full course of current longer therapy. If the study regimens are shown to be noninferior or superior to the control regimen, that would represent an even greater advance for patients with DS-PTB and TB control programmes globally. However, there are a few negative aspects that need to be considered before an FQ-containing first-line regimen could be broadly recommended. The FQs are fairly effective drugs for common nonspecific respiratory syndromes and community-acquired pneumonia, and curtailing this usage to ensure they remain effective as first-line TB drugs may not prove beneficial to all-cause morbidity and mortality at the community level. Also, using FQs as standard first-line therapy would reduce their effectiveness against MDR-TB, and could perhaps result in the emergence of more XDR-TB. Its implementation might be suggested only where the prevalence of Lfx-resistant TB is low and FQs are not routinely used for nonspecific respiratory symptoms when TB cannot be effectively excluded would reduce concerns above.

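### At the stated rates, 1300 patients per group give about 74 to 76% power after the plan's own losses, not the stated 80%

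*Protocol article*

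**What the plan says.** The Sample size assumption section of the protocol article gives every input and the result.

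- Control: "the standard 6-month regimen has a 95% or higher sputum culture conversion rate".
- Shortened regimens: "with estimated 92.5% of that for 4.5-month study regimen based on the published data".
- Margin: "a margin of noninferiority of 5% was used".
- Losses: up to 20% lost to follow-up or not assessable in the primary analysis, and "with the consideration of approximately 5.5% primary drug resistance prevalence".
- Result: "a total target sample size was 3900 patients (1300 subjects per group) would be required to demonstrate noninferiority, with a statistical power of 0.8", with alpha 0.05 one-sided.

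The Statistical analysis section sets the decision rule. The upper Wald limit at one-sided 5% for the difference in unfavourable outcomes must lie below 5%, in both the per-protocol (PP) and the modified intention-to-treat (mITT) populations. Allocation is 1:1:1 (Randomization and study regimens).

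Two other places bear on the resistance allowance. Study patients describes patients "with culture-confirmed susceptibility to H, R, E and Z and Lfx", and the Discussion reports that in a 2010 national survey "Lfx resistant TB accounted for 9.1% among new TB patients".

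**The concern.** The section presents 1300 per group as the number that gives 80% power after the losses have been allowed for. The standard formula with the same inputs needs 1,157 patients per group who can actually be analysed. That leaves room for a total loss of about 11%, while the section names losses of 20% or about 24%.

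The type I error, the margin and the analysis rule are not affected. What is at stake is how a negative result would be read. If a regimen fails to show noninferiority, readers will weigh that against a claimed 20% chance of missing a regimen that performs as assumed. On the plan's own figures that chance is about 24 to 26%.

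**Working it through.** **Inputs.** Control rate 0.95, shortened-regimen rate 0.925, margin 0.05, one-sided alpha 0.05 (z = 1.6449), power 0.80 (z = 0.8416), losses 20% and 5.5%, and 1300 per group, all from Sample size assumption. The unpooled Wald rule comes from Statistical analysis. I take the quoted conversion rates as the favourable-outcome rates for the primary comparison, because the section gives no others. I read 92.5% as an absolute rate. Read as a share of 95% it would be 0.925 × 0.95 = 87.9%, a gap of 7.1 points, which already exceeds the margin.

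**Assessable patients needed per group**

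- Variance term: 0.95 × 0.05 + 0.925 × 0.075 = 0.116875.
- Distance to the margin: 0.05 − 0.025 = 0.025.
- n = (1.6449 + 0.8416)² × 0.116875 / 0.025² = 1,156.1, so 1,157.

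**Attempt to reproduce 1300**

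| Allowance applied to 1,157 | Randomised per group |
|---|---|
| 20% only: 1,157 / 0.80 | 1,447 |
| Both, multiplied: 1,157 / (0.80 × 0.945) | 1,531 (4,593 in total) |
| Both, added: 1,157 / 0.745 | 1,554 (4,662 in total) |
| 20% only, as n × 1.2 | 1,389 |
| Both, as n × 1.255 | 1,453 |
| 5.5% only: 1,157 / 0.945 | 1,225 |

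None of these gives 1300. Other standard formulas raise the starting figure: 1,160 with pooled variance, 1,200 with Farrington-Manning, and about 1,235 with a continuity correction.

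**Power with 1300 per group**

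Power = Φ(0.025 / √(0.116875 / n) − 1.6449), where n is the assessable number per group.

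| Losses applied | n | Power |
|---|---|---|
| None | 1,300 | 83.9% |
| 5.5% only | 1,228.5 | 82.1% |
| 20% only (5.5% within it) | 1,040 | 76.2% |
| 20% and 5.5%, multiplied | 982.8 | 74.1% |
| 20% and 5.5%, added | 968.5 | 73.6% |

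For the fourth row: √(0.116875 / 982.8) = 0.010905; 0.025 / 0.010905 = 2.2925; 2.2925 − 1.6449 = 0.6476; Φ(0.6476) = 0.741. Simulating the Wald rule with 983 per group gives 74.0%.

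**Loss that 1300 can absorb.** 1,157 / 1,300 = 0.89, so 11%. The stated losses are 20%, or 1 − 0.80 × 0.945 = 24.4% for both.

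**Side calculation for levofloxacin.** With 9.1% in place of 5.5%: 1,300 × 0.80 × 0.909 = 945 assessable, power 72.7%.

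**The case against.** **The 20% is an upper figure.** This is correct. At 10% total loss 1,170 are assessable and power is 80.4%; at 15% it is 1,105 and 78.4%. The 74 to 76% is therefore the power at the planned allowance, not a forecast. The section nevertheless says that 1300 already covers that allowance, and it does not.

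**The 5.5% may not be a further loss.** Resistant patients may already be among those not assessable, or may be removed before randomisation. The wording does not settle this. It is why 76% has to be given beside 74%. Both are below 80%.

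**Other assumptions come near 1300.** Using the 95% variance in both arms gives 940 assessable, or 1,243 to 1,262 after both losses. Rates of 96% against 93.5% give 1,299 and 80.1% power, and the section does say 95% or higher. Either route may be where 1300 came from, but both abandon the stated 92.5%. With the control at 96% and the shortened regimen kept at 92.5%, power falls to about 42%.

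**Stronger readings that a reader might infer**

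- *The shortfall is a minimum, because both PP and mITT must succeed.* A joint requirement cannot raise power above that of the smaller set. But the 20% may already describe the PP set, last observation carried forward may keep lost patients in the mITT set, and actual loss may be below 20%. The article does not show that 74% is a ceiling on the trial's real power.
- *The 9.1% levofloxacin figure shows the 5.5% to be wrong.* The article does not say which drugs the 5.5% covers or how far the two figures overlap, and the sample size section does not use the 9.1%. The Discussion also cites a study in which fluoroquinolone resistance went with resistance to other drugs, which argues against simply adding the two. It is a sensitivity case only.

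**Conclusion.** The point holds for the stated power. At exactly 95% and 92.5%, with a 5% margin and one-sided 5% Wald testing, 1300 per group gives about 74% power when both losses apply and about 76% when the 5.5% falls within the 20%. The gap is 4 to 6 percentage points. It applies to one regimen compared with control in one analysis population.

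The conclusion does not depend on the choice of formula: at the stated rates, every standard version that applies the 20% loss needs more than 1300 per group. It does depend on taking the 20% at its stated upper value and the 92.5% as written. The levofloxacin figure is not part of the conclusion.

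**What to change.** Keep 1300 per group and correct the sentence in Sample size assumption, for example: with 1300 randomised per group and about 983 assessable after 20% loss and 5.5% resistance, power is about 74% (1,040 assessable and about 76% if resistance is counted within the 20%); 80% power requires 1,157 assessable patients per group. If other rates or another variance formula produced 1300, state them instead.

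In the same place, say whether the 5.5% is separate from the 20%, which drugs it covers and where it comes from. If it excludes levofloxacin, report the lower power as a sensitivity figure, about 73% with 9.1% in its place.

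The cost is a change of wording and a less favourable stated power. Enrolling more patients is optional; at the stated losses, 80% power would take about 1,447 per group (4,341 in total) if the 5.5% is within the 20%, or about 1,531 (4,593 in total) if both apply.
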